### Data collection methods

The patients will be asked to come in 2 months later for a follow up interview to assess the outcome of the trial. Data will be collected on a Data collection form (DCF) in this interview by a research officer who will be blinded to the allocation of the participants. This primarily consists of the MMAS and a tool that assesses patient satisfaction regarding the SMS innovation.

Participants in both arms will be contacted 2 days prior to interview as reminders for their appointment. They will be compensated for their fare for reaching the center. In case, the participants do not report for their follow up appointment, they will be contacted and their appointments will be rescheduled.

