## Methods

### Design overview (Fig. 1 (Study flow chart))

The SMS4stroke trial will be a randomized, controlled, assessor blinded single center superiority trial. The participants will be randomized into two parallel groups in a 1:1 ratio via block technique with one group receiving the standard of care as per institutional guidelines while the parallel group receiving SMS reminders for each dose of medicine in addition to the standard of care. The intervention group will also receive twice weekly SMS that reinforce healthy behaviors and the importance of taking medications.

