### Outcomes

The primary outcome of interest will be a change in medication adherence after 2 months of receiving the SMS. These findings will be compared to its corresponding findings from the control group to account for the Hawthorne effect.

Medication adherence will be measured at recruitment and after 2 months in both groups on the Morisky Medication Adherence Scale [18]. The scale has been used in a similar setting previously and it has been translated and validated in Urdu [41]. The change will be determined by comparing the score on the MMAS before and after the intervention.

The instrument consists of 8 questions and the response to each question is scored as either 0 or 1. The maximum score, hence, through this questionnaire is 8. A higher score indicates better adherence. A score of < 2 indicates low adherence.

Secondary outcome measures include patient satisfaction and acceptability of using an e-health based innovation such as the SMS to improve clinical outcome. This will be done through a tool that has been designed for IT based interventions and adapted for this study. This tool identifies beneficial and untoward attributes of the SMS for stroke intervention by users. The tool design for measuring acceptability of innovation is based on Roger's Diffusion of Innovations theory. The tool hence has questions that specifically assess the relative advantage of SMS, its compatibility with the study population, its complexity, its trialability and observability [42].

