### Participant timeline

Recruitment will begin with signing of an informed consent and assigning the patient an ID number. Data collection will begin with a detailed interview regarding the demographic and clinical details of the patient including his/her prescription details. The baseline MMAS score for each patient will also be calculated at this time. This will be followed by the research staff leaving the room and a senior investigator (QS) taking over at which point the patient will be randomized to either the intervention or the control group by the independent CTU staff.

If the patient is allocated to the intervention arm, the investigator (unblended) will explain the details of the intervention and will demonstrate by sending one test SMS on his/her cell phone (in English and Urdu both).

If there is a change in patient prescription with respect to any drug or dose by any physician, the patient will be requested to notify at a 24 hours helpline number answered by trained staff. In addition, since participants are tagged in the hospital system as trial participants all visits are logged and there will be tracking to ascertain any changes in prescription which will be medically confirmed.

Following the recruitment visit, the patients will not be required to come back to clinic for any additional visits for the purposes of this study for 2 months at which time there will be a follow up interview. At this time, patient adherence will be assessed by the research officer again who will be blinded.

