### Data management

Research officers will be specifically trained to collect all data during patient interview leaving no data collection forms incomplete. All data collected will be sent to the research office in sealed envelopes. At the end of each day, any missing data on forms will be noted. In case, of missing data, the participant will be contacted to fill the missing information. The data will be entered by a separate team that is formed for data entry on Microsoft Access. This team does not include any members involved with research. As per institutional policy, double entry is mandatory for all data. The data entry operators will be blinded to the allocation of each patient. All data entered will be backed up centrally.

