### Ethics and human subjects protection

All patients taking part in the trial will be required to provide written informed consent at the time of recruitment. Consent forms will be approved by the ERC and they will be available in English and Urdu. The participants will have the right to withdraw at any moment during the study; their inclusion or exclusion from the study will not affect the usual standard care provided to them. In addition, all participants will be provided financial reimbursement for all costs pertaining to follow up visits and replying to reminder SMS. Participants identified with depression and dementia will be referred to appropriate physicians for further management.

In addition, special care will be taken to maintain the confidentiality of the patient's disease. The name of the institution sending the SMS will not be mentioned in the SMS, nor will be the patient’s name. In addition, special care will be taken to send the health promotional texts twice weekly at times that do not cause discomfort to the patient such as late at night.

In days of high security alerts in the city and announced SMS blackouts, it is planned to send advance SMS the night before to the participant that there would not be any SMS the next day to avoid participant anxiety or uncertainty about continuity of care or reception of services.

All staff has received Good Clinical Practice (GCP) training and a face to face training in a 2 day Neuroethics course regarding research in the developing world where all design aspects for this trial were discussed.

The study is approved by the Ethical Review Committee of the Aga Khan University, Karachi, Pakistan. The study Ethical Review Number is 2763-Med-ERC-13. Any changes to the protocol need to be approved by the ERC before implementation. Monthly reviews on the progress of the trials will be conducted by the ERC including inspection of signed informed consent forms. Although the trial is intended to last around 3 months, in case trial duration exceeds 6 months, the ERC will require the protocol to be resubmitted for review.

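### The blinded officer collects the MMAS and the SMS-satisfaction tool in one interview on one form, so the assessor blinding claimed for the primary outcome is not protected

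*Protocol article*

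**What the plan says.** All references are to the protocol article.

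- **Design overview** makes the claim: "The SMS4stroke trial will be a randomized, controlled, assessor blinded single center superiority trial". The Discussion counts blinded assessment among the study's strengths.
- **Participant timeline** applies it to the 2-month visit: "At this time, patient adherence will be assessed by the research officer again who will be blinded".
- **Data collection methods** says how that visit runs: "Data will be collected on a Data collection form (DCF) in this interview by a research officer who will be blinded to the allocation". The next sentence gives the content: "This primarily consists of the MMAS and a tool that assesses patient satisfaction regarding the SMS innovation".
- **Outcomes** describes the second instrument: "This tool identifies beneficial and untoward attributes of the SMS for stroke intervention by users". Its questions are built on the attributes in Rogers' diffusion theory.
- **Intervention group** sends dose reminders and twice-weekly health messages to that arm alone. Under **Control group**, the only messages described are the centre's routine appointment reminders.
- **Data management** has missing items noted at the end of each day and the participant contacted to supply them. It also says of the people who key the forms: "The data entry operators will be blinded to the allocation of each patient".

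**The concern.** The person described as blinded is given an instrument that makes sense only for one arm, at the same sitting and on the same form as the primary outcome. The article itself assigns both tasks to that person, so this is not a detail lost in condensing a longer protocol.

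The primary outcome is an adherence score obtained at interview from participants who know their allocation. The Discussion names self-report as the major limitation. Assessor blinding is meant to stop the interviewer adding a further bias through prompting, clarification or the coding of doubtful answers. If the interviewer can learn the arm before the score is final, that safeguard is weakened on the endpoint that decides the trial.

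The design takes care over this elsewhere. Under Participant timeline, research staff leave the room before randomisation and another investigator explains the intervention. The follow-up visit has no matching separation.

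**Working it through.** **Does the tool reveal the arm?** The article does not say whether controls are asked the tool, so both cases need checking.

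1. Tool given to intervention participants only: whoever gives or skips it must know, or find out, the arm.
2. Tool given to everyone: controls have had no study messages to rate, and their answers will show it.

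In either case the officer can infer the allocation once the tool is opened.

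**Is the MMAS final by then?** The sections give this picture:

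| Point | Stated? |
|---|---|
| Order of the two instruments | No; the MMAS is merely named first |
| MMAS signed or closed before the tool | No |
| A different person for the tool | No; one officer is named |
| A separate form | No; one data collection form |
| Later completion of missing items | Yes (Data management), without saying by whom |

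If the MMAS always comes first, its initial score precedes the disclosure. Nothing requires that order, and items missing from the MMAS could still be completed after the arm is known.

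**Sample-size inputs (Sample size section; 86 per arm in the Abstract).** Difference 1, SD 2, two-sided 5%, power 90%, 172 in total.

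The plan's own figure first: n per arm = 2 × SD² × (1.960 + 1.282)² / difference² = 2 × 4 × 10.51 / 1 = 84.1, rounded up to 85. The t-test solution is 85.03, rounded up to 86, so 172 in total. The stated figure reproduces.

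**Illustration of what a shift would do.** The documents give no size for interviewer bias. The shifts b below are assumptions, with no true effect.

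- SE = 2 × √(2/86) = 0.305.
- Smallest significant difference = 1.96 × 0.305 = 0.60 points.
- P(reject) = Φ(b/SE − 1.96) + Φ(−b/SE − 1.96).

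| Assumed shift b | b/SE | Two-sided rejection rate |
|---|---|---|
| 0 | 0 | 5% |
| 0.1 | 0.33 | 6% |
| 0.25 | 0.82 | 13% |
| 0.5 | 1.64 | 37% |

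The textual finding does not depend on this table.

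**The case against.** The strongest reply concerns order. What matters is whether the officer knows the arm when the MMAS is scored. The MMAS is named first, and if it is done first the score is already recorded. The order of sections on a form is also the sort of detail a full protocol may hold. This stands in part: one cannot say that every MMAS score is taken unblinded. It does not remove the point, because the article itself puts both instruments with one blinded person and separately allows later completion of missing items.

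Several stronger readings are tempting and are not supported:

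- *Blinding is defeated, or fails for every intervention participant.* That depends on an order the article does not give.
- *Assessor blinding is the only safeguard against interviewer bias.* The MMAS is a fixed set of 8 items scored 0 or 1 and validated in Urdu, and the officers are trained. Both limit interviewer discretion.
- *Reimbursement discloses the arm.* The ethics section says "all participants will be provided financial reimbursement for all costs pertaining to follow up visits and replying to reminder SMS", and only one arm replies to reminders. It does not say that the officer handles this or that it is settled at the interview, so no route to unblinding is shown.
- *Data-entry unblinding biases the outcome.* The operators could infer the arm from the form, which conflicts with the stated blinding. But they key answers already recorded, with double entry, so the threat to the primary outcome is small.

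The error rates rest on assumed shifts. On a scale of eight 0/1 items, 0.5 points means a net one-item change in half of the intervention participants, which is demanding if the MMAS comes first.

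**Conclusion.** The point holds in a limited form. As written, the procedure lets the blinded assessor learn the arm within the outcome interview, and nothing stated ensures that the MMAS is final before then. The blinding claimed under Design overview, Participant timeline and Discussion is therefore unprotected for the primary outcome; it is not shown to have failed.

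This rests on two readings of the text: that the tool concerns the study messages, and that only the intervention arm receives them. Both are stated. The size of any bias is unknown, and the range of about 6% to 37% for the false-positive rate illustrates assumed shifts of 0.1 to 0.5 points; it is not an estimate. The sample size is unaffected. Because the fault lies in a stated procedure for the primary endpoint and is cheap to remove, it should be corrected.

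**What to change.** Amend Data collection methods and Data management to state that:

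1. The blinded officer completes, signs and closes the MMAS, including any missing items, before anything about messages is raised.
2. Participants are asked beforehand not to mention messages during that interview.
3. The acceptability tool is on a separate form, given afterwards to intervention participants only, and is either self-completed or taken by the investigator who is already unblinded.
4. The two forms are keyed separately, so that the blinding stated for data entry also holds.

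The cost is a form split and a slightly longer visit with a hand-over. No new staff are needed, and the endpoint and sample size do not change. The change removes the interviewer's contribution only. Bias from participants who know their arm and report their own adherence remains and should stay listed as a limitation.

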### Pilot testing

Pilot Testing will be performed on 10 % of the sample size i.e. 20 patients before commencement of the study. As per the actual study, participants will be recruited from Neurology and Stroke Clinics and standard procedures will be followed. This will allow testing the intervention for smooth application and any systematic errors. Problems (if any) with eligibility criteria will be identified and the feasibility of achieving sample size will be assessed. The data collection tool will be assessed for flow of questions and comprehensiveness. The intervention will be assessed for practicality relating to delivery, accuracy, timeliness, comprehension and satisfaction. These participants will be excluded from the final study sample.

### Data management

Research officers will be specifically trained to collect all data during patient interview leaving no data collection forms incomplete. All data collected will be sent to the research office in sealed envelopes. At the end of each day, any missing data on forms will be noted. In case, of missing data, the participant will be contacted to fill the missing information. The data will be entered by a separate team that is formed for data entry on Microsoft Access. This team does not include any members involved with research. As per institutional policy, double entry is mandatory for all data. The data entry operators will be blinded to the allocation of each patient. All data entered will be backed up centrally.

### Statistical methods

Analysis will be performed using the intention to treat principle at two stages: interim analysis after 25 % of the sample has been reached and final analysis after data has been collected from all study participants. The analysis will be reported to the project team who will publish the results in a timely manner. Descriptive statistics will be reported as mean (with standard deviation) for continuous variables like age, years of schooling, years since diagnosis, MMAS score etc. Proportions will be reported for categorical variables like gender, marital status, area of residence, employment status, proportion of patients with depression etc.

The primary endpoint will be the difference in medication adherence level between the two groups as detected by the MMAS after 2 months of the intervention.

The acceptability and patient satisfaction of the intervention will be reported through proportions with a break up for Roger’s factors. In addition, we will be monitoring the study for participant ‘alert fatigue’ and withdrawals from the intervention.

All data analysis will be performed on STATA version 12. We plan to apply regression modeling techniques to control for confounders or other covariates such as baseline clinical status as calculated by the Modified Rankin Scale, patient age, the severity of their stroke, number of medications, caregiver or stroke survivor cell phone user are all important variables that will be included in the data analysis as to how they affect adherence. Sensitivity analyses are planned for caregiver SMS recipient vs. direct users for response rates to the intervention.

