### Sample size

Based on literature, we estimated the mean MMAS score to be 6 [43] in the control arm and 7 in the intervention group, giving a mean difference of 1. A standard deviation of 2 is assumed for this score. Using these values, a sample of at least 172 subjects will be required to achieve a power of 90 % and significance level of 5 % when testing a two tailed hypothesis. This translates into 16 % effect size as hypothesized. Keeping a 15 % attrition rate the sample size was inflated so that at least 100 subjects will be targeted for each arm in the sample.

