### Assignment of interventions

Cards with patient assignments to either the intervention or the control group will be prepared by the CTU through computerized block randomization technique in block sizes of 10. This is to ensure similarity between the two groups at all times permitting interim analysis during the study. Additionally block size was not discussed with the research team interacting with participant recruitment to limit predictability of assignment and researcher bias.

The randomization cards will be sealed in opaque envelopes, marked by ID and kept with the CTU. Even if the envelope is held against bright sunlight one will not be able to ascertain the allocation. After enrollment, obtaining informed consent and completing the baseline measurements, the CTU will be informed and randomization of the participant will be done.

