### Access and dissemination policy

Only the PI and research team will have access to the study results who will be responsible for publishing in a timely manner. The funding source will not have any special access or privileges regarding results before publication. However since this study is funded by NIH , all publications will be open access in PubMed Central as per NIH policy [44].

The ERC and the CTU will be provided access if required. Safety issues and adverse events will be reported to the ERC of the Aga Khan University.

Results will be disseminated through scientific journals, conferences and meetings. They will be available at https://clinicaltrials.gov as soon as they are finalized. They will also be shared with concerned departments and patients.

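### The 25 % interim analysis appears to be between arms and is reported to the project team without being separated from the final analysis; it should be pooled, or held by the independent CTU

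*Protocol article*

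**What the plan says.** Under Statistical methods, the protocol article plans one kind of analysis twice: "Analysis will be performed using the intention to treat principle at two stages: interim analysis after 25 % of the sample has been reached", and again at the end, once outcomes are in for everyone. The next sentence names the recipient: "The analysis will be reported to the project team who will publish the results in a timely manner". It does not distinguish interim from final results.

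Under Assignment of interventions, the block size of 10 is explained as follows: "This is to ensure similarity between the two groups at all times permitting interim analysis during the study".

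Under Access and dissemination policy: "Only the PI and research team will have access to the study results". The ethics committee and the clinical trials unit (CTU) get access only if required. Study setting describes the CTU as independent.

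Under Sample size there is a single error level: "a sample of at least 172 subjects will be required to achieve a power of 90 % and significance level of 5" %, two-tailed, for a difference of 1 point on the MMAS with SD 2. Duration says that the trial continues until the sample size is reached and the 2-month follow-up is complete. No section gives a purpose for the interim analysis, an interim test or a stopping rule.

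**The concern.** Two things are at stake.

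**Who sees the arm difference.** The primary outcome is self-reported adherence, which the Discussion names as the major limitation of the study. The trial has one centre, and an unblinded senior investigator explains the intervention to participants. Staff also telephone intervention participants who have not replied for 5 days, rebook missed follow-up visits and recontact participants about missing data. Knowing the direction of the interim result could colour that conduct. The article relies on blinded assessment to protect the outcome, but nothing in it keeps the interim comparison away from the people running the trial.

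**How the 5 % is used.** The sample size is for one test at full size. If the same test were also run at 25 % of the sample at the same level, and a positive result at either stage counted, the overall false-positive rate would exceed 5 %.

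**Working it through.** **Inputs.** Difference 1, SD 2 (standardised difference 0.5), two-sided 5 %, 90 % power, 172 evaluable, 15 % attrition and 200 randomised (Sample size, Abstract); 1:1 allocation (Design overview); interim at 25 % of the sample (Statistical methods).

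**1. The plan's own figure.** By the normal formula, n per arm = 2 × (1.960 + 1.282)² × 2² / 1² = 84.1, so 85 per arm and 170 in all. The t-test version gives 85.03, rounded up to 86 per arm and 172 in all. The stated 172 is therefore reproduced as a single-look design: t-test power at 86 per arm is 90.3 %. It contains no allowance for an interim test.

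**2. Is the interim between arms?** This is an inference, and three places support it:
- Statistical methods applies intention to treat, a rule about analysing by randomised arm, at both stages.
- Assignment of interventions wants the two groups alike at all times so that an interim analysis is possible. That balance matters only if the groups are compared.
- Feasibility already has its own vehicle, the 20-patient pilot, whose participants are excluded from the study sample.

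**3. What the look could show.** 25 % of 200 is 50, or 25 per arm.
- Standard error of the difference = 2 × √(2/25) = 0.566.
- 95 % CI half-width = t(48) × 0.566 = 2.011 × 0.566 = 1.14 points, wider than the 1-point target.
- Power for 1 point = 41 % by t-test (42 % by the normal approximation).
- With 15 % attrition, about 21 per arm: half-width 2.021 × 0.617 = 1.25 points, power 35 %.

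**4. Type I error.** At information fraction 0.25, the interim and final statistics have correlation √0.25 = 0.5. The overall error is 1 − P(|Z₁| < c₁ and |Z₂| < c₂).

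| Use of the interim | Interim level | Final level | Overall error |
|---|---|---|---|
| No efficacy claim | none | 0.05 | 5.0 % |
| Both stages tested | 0.05 | 0.05 | 9.07 % |
| Strict interim, final unadjusted | 0.001 | 0.05 | 5.06 % |
| Strict interim, final adjusted | 0.001 | 0.0494 | 5.00 % |

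A simulation of 200,000 trials with t-tests at 25 and 100 per arm gave 9.08 % for the second row. The second-row figure is 9.2 % at a fraction of 0.20 and 9.0 % at 0.29 (50 of 172), so it hardly depends on how 25 % is counted.

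**The case against.** The strongest reply is that the article does not establish a 9 % error rate. That stands. No section states a significance test at the interim or a possible early claim, and Duration has the trial run to full sample size. A boundary could also be in an analysis plan that is not shown, so its absence is not a finding.

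The comparative nature of the look can also be disputed. The interim is triggered when 25 % of the sample has been reached, which could mean 50 enrolled rather than 50 with 2-month outcomes. The rationale for the blocks still points to a between-group look, though not necessarily to a test of the 2-month MMAS.

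On reporting, the link to publication could mean that only final results go to the team. The text does not say so, and the access policy does not separate the stages either.

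A reader might infer that the outcome assessors would see the interim result. The documents do not support that: the project team is not defined, the 2-month MMAS is taken by a research officer blinded to allocation, and an aggregate difference would not reveal any participant's arm. Message delivery is also partly protected, since reminders are automated and each health-message set is selected at recruitment.

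A reader might also infer damage to recruitment. Under Ethics and human subjects protection the article says "Although the trial is intended to last around 3 months". With 2 months of follow-up, that leaves about 3 − 2 = 1 month for recruitment, which would finish before the first 2-month outcomes exist. Only a longer trial, for which the same section provides, would still be recruiting when the result arrived. Harm to recruitment is therefore possible but not shown.

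**Conclusion.** The point holds as a defect of routing and purpose. The article fixes an analysis at 25 % that is most naturally read as between arms, and names the project team as recipient without separating it from the final analysis. In a single-centre trial with a self-reported outcome, that allows the arm difference to be seen mid-trial. The look offers little in return: about 41 % power and a half-width of about 1.14 points at 25 per arm, assuming 50 participants with outcomes and the planned SD of 2.

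The false-positive rate is a conditional risk, not an established property of the plan. It is 5 % if no efficacy claim is made at the interim, and about 9.1 % if both stages are tested at two-sided 5 % and either can count. The article does not say which applies, so the stronger statement that the plan inflates type I error to 9 % should not be made.

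**What to change.** In Statistical methods, define the 25 % look as a pooled check of recruitment, SMS delivery, attrition and data quality, with no comparison of arms and no efficacy claim. State that only the final comparison is reported to the project team, and align Access and dissemination policy with this. The final test then keeps the full 5 %.

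If a comparative look is kept, the independent CTU should hold it, arm results should be withheld from trial staff, and the levels should preserve 5 % overall, for example interim p < 0.001 with final p < 0.0494. Keeping the final level at 0.05 beside that interim level would give 5.06 %.

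The cost is small. The CTU already exists and the sample size is practically unaffected. The team gives up early comparative results, and because the trial is ongoing, the change needs ethics committee approval before it is implemented.

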**Methods:**

This will be a randomized, controlled, assessor blinded single center superiority trial. Adult participants with access to a cell phone and a history of stroke longer than 1 month on multiple risk modifying medications will be selected from Neurology and Stroke Clinic. They will be randomized into two parallel groups in a 1:1 ratio via block technique with one group receiving the standard of care as per institutional guidelines while the parallel group receiving SMS reminders for each dose of medicine in addition to the standard of care. In addition intervention group will receive messages for lifestyle changes, medication information, risk factors and motivation for medication adherence. These will bemodeled on Social Cognitive Theory and Health Belief Model and will be categorized by Michies Taxonomy of Behavioral Change Communication. Patient compliance to medicines will be measured at baseline and then after 2 months in each group by using the Morisky Medication Adherence Scale. The change in compliance to medication regimen after the intervention and the difference between the two groups will be used to determine the effectiveness of SMS reminders as a tool to increase medication compliance. The acceptability of the SMS will be determined by a tool designed for this study whose attributes are based Rogers Diffusion of innovation theory.

A sample size of 86 participants in each arm will be sufficient to detect a difference of 1 point on the MMAS with a power of 90 % and significance level of 5 % between the two groups; using an attrition rate of 15 %, 200 participants in all will be randomized.

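### The primary outcome is stated as a change in MMAS, as the 2-month level, and as both; one analysis of the 2-month score adjusted for baseline MMAS should be named throughout

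*Protocol article*

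**What the plan says.** The protocol article describes the primary outcome in three places.

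- **Outcomes:** "The primary outcome of interest will be a change in medication adherence after 2 months of receiving the SMS". The section adds: "The change will be determined by comparing the score on the MMAS before and after the intervention". It also says that the findings will be set against those of the control group.
- **Statistical methods:** "The primary endpoint will be the difference in medication adherence level between the two groups as detected by the MMAS after 2 months".
- **Abstract, Methods:** "The change in compliance to medication regimen after the intervention and the difference between the two groups will be used to determine the effectiveness".

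The Sample size section works with scores, not changes: "we estimated the mean MMAS score to be 6 [43] in the control arm and 7 in the intervention group, giving a mean difference of" (the figure stated is one point). It continues: "A standard deviation of 2 is assumed for this score". From these inputs, "a sample of at least 172 subjects will be required to achieve a power of 90 % and significance level of 5" %, two-sided. The section gives no SD of change and no correlation between baseline and 2-month scores.

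Under Participant timeline, the baseline MMAS is obtained at the recruitment interview, before randomisation. For adjustment, Statistical methods plans "regression modeling techniques to control for confounders or other covariates such as baseline clinical status as calculated by the Modified Rankin Scale", and goes on to name age, stroke severity, number of medications and whether the phone user is the caregiver or the patient. Baseline MMAS is not among the named variables.

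**The concern.** A difference in change and a difference in 2-month level are separate test statistics. On the same data they can give different p-values, because they have different variances and treat chance baseline imbalance differently. While the text supports both, the choice between them could be made after the data are seen. The Abstract's wording, which judges effectiveness on the two together, does not settle it.

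The sample size also matches only one of them as written. Its power statement carries over to the change score only under a condition on r that the article does not mention.

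Finally, the baseline value of the outcome is normally a useful predictor of its follow-up value. Here it is measured on everyone before randomisation, yet it is not named for the model.

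**Working it through.** **Inputs from the Sample size section and the Abstract.** Means 6 and 7, so difference δ = 1; SD σ = 2; two-sided 5 %; power 90 %; 86 per arm. With 15 % attrition from 200 randomised, 200 × 0.85 = 170 remain, or 85 per arm.

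**Assumptions not in the documents.** SD 2 at baseline as well as at 2 months; correlation r between the two scores, shown from 0.2 to 0.7.

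**Step 1: reproduce the plan's figure.** n per arm = 2σ²(1.960 + 1.282)²/δ² = 2 × 4 × 10.51 = 84.1, rounded up to 85. The t-test version needs 85.03, so 86 per arm and 172 in total, as stated. The t-test power is 90.3 % at 86 per arm and 90.0 % at 85. The stated power is correct for an unadjusted comparison of 2-month levels, whatever r is.

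**Step 2: SD under each analysis.**

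- Change score: the variance is σ² + σ² − 2rσ², so SD = 2√(2(1 − r)).
- 2-month score adjusted for baseline (ANCOVA): residual SD = 2√(1 − r²).

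**Step 3: power.** Power = Φ(δ / (SD√(2/n)) − 1.960). Example at r = 0.2 and n = 86 for the change score: SD = 2√1.6 = 2.530; standard error = 2.530 × √(2/86) = 0.386; 1/0.386 − 1.960 = 0.63; power 73.6 %.

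| r | Change SD | Power, 85 / 86 per arm | ANCOVA SD | Power, 85 / 86 per arm |
|---|---|---|---|---|
| 0.2 | 2.530 | 73.1 / 73.6 % | 1.960 | 91.4 / 91.7 % |
| 0.3 | 2.366 | 78.7 / 79.1 % | 1.908 | 92.7 / 93.0 % |
| 0.4 | 2.191 | 84.5 / 84.9 % | 1.833 | 94.5 / 94.7 % |
| 0.5 | 2.000 | 90.3 / 90.6 % | 1.732 | 96.4 / 96.6 % |
| 0.6 | 1.789 | 95.4 / 95.6 % | 1.600 | 98.3 / 98.4 % |
| 0.7 | 1.549 | 98.8 / 98.8 % | 1.428 | 99.5 / 99.6 % |

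These are normal approximations; the t-test values are lower by about half a percentage point or less.

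**Step 4: compare the analyses.** The change score equals the level in precision at r = 0.5, is worse below it and better above it. ANCOVA is at least as precise as the level, since 1 − r² ≤ 1. It is also at least as precise as the change score, since 1 − r² = (1 − r)(1 + r) ≤ 2(1 − r). Against the unadjusted level, the gain is equivalent to a sample larger by the factor 1/(1 − r²): 1/0.75 = 1.33 at r = 0.5 and 1/0.51 = 1.96 at r = 0.7. The one degree of freedom spent on the covariate is ignored.

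**The case against.** The strongest reply is that the two sections that fix the analysis agree. Statistical methods names the 2-month level, the Sample size section powers that level, and the figure reproduces. A reader might infer that the 90 % claim is wrong. It is not: a shortfall needs both that the change score is analysed and that r is below 0.5. Above 0.5 the change score has more power than stated.

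A reader might also infer that effectiveness will be judged on a before-after change within the SMS arm. The documents do not support that. Outcomes compares the change with control, and the Abstract pairs the change with the difference between the groups.

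Nor is baseline MMAS excluded. The covariates are introduced as examples, and a fuller plan that is not shown could add it. An unadjusted comparison of levels would still be valid, so adjustment is an improvement and its absence is not an error.

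Lastly, because baseline is measured before randomisation, change and level have the same expected between-arm difference. They share instrument, time point and comparison, so the freedom to choose between them is limited.

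All of this stands, and it narrows the point. It does not remove the conflict: the current text still gives the primary outcome in different forms, with different precision and possibly different p-values.

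**Conclusion.** The inconsistency is real and should be resolved. The sample size arithmetic is right, and about 90 % power holds for the 2-month level. If the change score were the primary analysis, power at 85 to 86 per arm would run from about 73 to 74 % at r = 0.2 to about 99 % at r = 0.7, crossing 90 % at r = 0.5. Adjusting the 2-month score for baseline MMAS keeps power at about 90 % or more for any r. These figures rest on a true difference of 1, SD 2 at both times, and a range of r that is assumed because the documents give none. The remedy is a free improvement that also settles the conflict; it does not repair a failed power calculation.

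**What to change.** State one primary analysis in the same terms in the Abstract, Outcomes, Sample size and Statistical methods: the between-arm difference in mean 2-month MMAS score, estimated from a linear model with treatment and baseline MMAS. Fix in advance which of the other listed baseline covariates enter that model. Report change from baseline descriptively. The Sample size section can keep 172, with a sentence saying that it is computed for the unadjusted 2-month score and that adjustment for baseline MMAS is expected to maintain or raise the power.

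The cost is a wording amendment, made before between-arm results are seen. Under the article's own rule it needs ethics committee approval. Baseline MMAS is already collected, so no new data and no extra patients are required. The model also takes account of chance imbalance in baseline adherence.
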